## Abstract

**Background:**

Recent evidence proved the necessity to improve health care and pain management in newborns. Osteopathic manipulative treatment (OMT) has been largely used to treat painful syndromes as well as term and preterm newborns. Recent studies have demonstrated positive results of osteopathy in reducing length of stay and costs. However, no trials were carried out on pain in newborns. The aim of the present clinical trial is to explore the effectiveness of osteopathic treatment in reducing pain in a sample of preterms.

**Methods/design:**

A three-armed single blinded placebo-control randomised controlled trial protocol has been designed to primarily evaluate the extent to which OMT is effective in reducing pain in preterms. One hundred and twenty newborns will be enrolled from one tertiary neonatal intensive care unit in central Italy and randomised in three groups: study, sham and control. The study group will be further prospectively randomised in two subgroups: experienced osteopaths and students. All preterms will receive standard medical care. Osteopathic treatment will be applied to the study group only whilst ‘soft touch’ will be administer to the sham group only. Newborns will undergo manual sessions once a week for the entire period of hospitalisation. Blinding will be assured for neonatal staff and outcome assessor. Primary outcome will be the mean difference in baseline score changes of PIPP questionnaire between discharge and entry among the three groups. Secondary outcomes will be: mean difference in length of stay and costs between groups. Statistical analyses will use per-protocol analysis method. Missing data will be handled using last observation carried forward imputation technique.

**Discussion:**

The present single blinded randomised controlled trial has been designed to explore potential advantages of OMT in the management of newborns’ pain. Currently, based on a patient-centred need-based approach, this research will be looking at the benefit of osteopathic care rather than the efficacy of a specific technique or a pre-determined protocol.

**Trial registration:**

The protocol has been registered on ClinicalTrials.gov (NCT02146677) on 20 May 2014.

## Background

Worldwide public health policies are paying considerable attention to prematurity and neonatal outcomes [1]. To date, the prevalence of neonatal short-term and long-term complications are high [2] even more if prematurity is considered [3-5]. Interestingly, several studies have been published recently considering pain in neonates as one factor associated with immediate [6,7] and long-term consequences [3]. Laboratory research has confirmed these results, highlighting that early repeated tissue injuries alter somatosensory and nociceptive pathways producing central and peripheral sensitisation [8].

Recent evidence proved the necessity to improve health care and pain management in newborns [9]. During the last three decades, the attempt to assess and report pain in neonates has resulted in the development of dozens of measurements [9]. The majority of these tools based its assessment on behavioural, contextual and physiological indicators. However, for a large proportion of these instruments lack of construct validity and reliability are reported. The only tools which have also been largely validated in clinical settings are the Behavioural Indicators of Infant Pain Scale [10] and the Premature Infant Pain Profile (PIPP) [11]. The PIPP was consistently used in clinical neonatal settings and research context providing a reliable tool for neonatal pain assessment [12].

Osteopathic manipulative treatment (OMT) has been used to treat term and preterm newborns. Recent studies demonstrated the effectiveness of OMT in reducing length of stay (LOS) and costs [13] as well as the likelihood of gastrointestinal episodes [14]. Moreover, the absence of adverse events and side effects was widely reported, thus considering the approach to be safe [13,15].

OMT has been extensively used to treat, prevent and manage pain symptoms. Numerous research has been published addressing acute and chronic pain in different medical conditions [16-18]. However, no trials have been carried out on pain in newborns. The aim of the present clinical trial is to explore the effectiveness of OMT in reducing pain in a sample of preterms.

## Methods/design

The current protocol is designed for a single blinded placebo-control randomised controlled trial (RCT) aiming at evaluating the extent to which OMT is effective in reducing pain in preterms. Secondary objectives will be reduction of LOS and cost-effectiveness.

From 5 May 2014 to 30 September 2015 newborns will be enrolled in the study at one tertiary neonatal ICU (NICU). Newborns will enter and be randomised only after parents or guardians have given written informed consent.

Infants who are admitted to the NICU will be eligible for inclusion. Inclusion criteria are: being born in Pescara’s hospital, having a gestational age (GA) between 29 and 37 weeks, being of either gender and without clinical and/or congenital complications. Exclusion criteria will be applied as follows: lack of guardian consent, having a gestational age > 37 weeks, being a newborn with HIV and from HIV seropositive/drug-addicted mother, being transferred to/from other hospital, the presence of any congenital or genetical disease, neoplasms, neurological, cardiovascular, urinary, haematological abnormalities, proven or suspected necrotising enterocolitis or abdominal obstruction, birth trauma, surgical patients, pneumoperitoneum, atelectasis, respiratory distress.

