### Randomisation and masking

Patients will be randomly assigned in a 1:1:1 ratio to either the OMT, the sham or the control group (Figure 1). Newborns will be eligible for randomisation from the first day of life. Block randomisation will be performed according to a computer-generated randomisation list using a block size of nine, and stratified by OMT group.

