### Data entering and data export

Data will be collected using an *ad-hoc* platform already used in previous studies [13,20,21]. Medical records will be acquired daily by the NICU staff.

Osteopathic records will be reported once a week when the osteopathic service is provided.

Maternal data will be also include collecting the following information: type of delivery, foetal presentation, whether placental abruption, pregnancy complications, single versus multiple gestation, whether premature rupture of membranes and any other complication.

Neonatal data will be gathered using the following parameters: gender, GA, birth weight, infants small for GA, neonatal complications (diagnosed at birth and during hospitalisation), diagnosis-related group (DRG) at discharge and reasons for drop out, if any.

A monitoring board will be organised and periodically will review the safety of data according to survival rate at discharge and relative risk of developing any clinical complication. The group sequential method will be utilised to define the rate at which type I errors occur; the Lan-DeMets generalisation of the O’Brien-Fleming boundary will be chosen. Interim analyses will be performed. Moreover, the monitoring board will be in charge of data export.

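### Transfer to another hospital is listed as an exclusion criterion although it is normally known only after randomisation, so applying it would remove randomised infants

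*Protocol article*

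**What the plan says.** The eligibility text under Methods/design first requires birth in the study hospital and infants "without clinical and/or congenital complications". It then introduces the exclusions with "Exclusion criteria will be applied as follows". The list includes "being transferred to/from other hospital" and ends with "proven or suspected necrotising enterocolitis or abdominal obstruction, birth trauma, surgical patients, pneumoperitoneum, atelectasis, respiratory distress". No time point is attached to any item.

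The same section says "Newborns will enter and be randomised only after parents or guardians have given written informed consent". Randomisation and masking adds "Newborns will be eligible for randomisation from the first day of life".

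Under Outcomes, the primary outcome is the PIPP change from entry to discharge. LOS, cost and the risk of adverse events are secondary.

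On the analysis set, the Abstract names per-protocol only, while Statistical analysis names per-protocol and intention-to-treat together as primary. Data entering and data export collects complications diagnosed during the stay as well as at birth, and has the monitoring board review "survival rate at discharge and relative risk of developing any clinical complication".

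**The concern.** An exclusion criterion protects the randomised comparison only if it is settled before allocation. Transfer out is normally a later event. If it excludes an infant, the infant leaves after the arm has been assigned and, usually, after treatment has begun. The arms that remain are then no longer guaranteed to be comparable.

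Every main outcome runs to discharge: PIPP change, LOS and cost. An infant transferred out mid-stay is therefore lost to all of them, and any adverse events in that infant may be lost as well. The per-protocol analysis gives this a direct route into the results, because an infant who meets a stated exclusion criterion would ordinarily fall outside that set.

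**Working it through.** **Step 1. When can each criterion be known?**

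- *Transfer from another hospital:* known at entry, but largely redundant, because birth in the study hospital is already required.
- *Transfer to another hospital:* normally seen only after entry. A transfer already arranged at screening could be applied then; an unplanned one could not. This is the working content of the criterion.
- *Enterocolitis, obstruction, surgery, pneumoperitoneum:* can be present or absent at screening and can also arise later. The text does not say which is meant.
- *Guardian consent, gestational age, maternal HIV or drug status, congenital or genetic disease, birth trauma:* baseline by nature.

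Randomisation may take place as early as the first day of life, after consent. That is an earliest time and not a fixed day. The argument on transfer out needs only that randomisation comes before discharge.

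**Step 2. How much loss does the sample size absorb?**

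Inputs from Statistical analysis: f = 0.30, α = 0.05, power 0.80, three groups, 37 per group raised to 40. Method: one-way ANOVA omnibus F test with N = 3n, noncentrality N × f², and degrees of freedom 2 and N − 3.

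- n = 36: 108 × 0.09 = 9.72, power 0.7916.
- n = 37: 111 × 0.09 = 9.99, power 0.8035. The stated 37 is reproduced.
- n = 40: 120 × 0.09 = 10.8, power 0.8359.

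The allowance is 1 − 37/40 = 7.5%, or three infants per group. The article gives no expected loss rate. Over an assumed range:

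| Removed per group | n left | Power |
|---|---|---|
| 5% | 38 | 0.815 |
| 7.5% | 37 | 0.804 |
| 10% | 36 | 0.792 |
| 15% | 34 | 0.766 |
| 20% | 32 | 0.738 |

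**Step 3. How would bias arise?**

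Let e1 and e0 be the shares removed in the OMT arm and a comparison arm. Let D be the mean difference between removed and retained infants, taken as equal in both arms. With no true effect the full arm means are equal, and each retained mean equals the full mean minus e × D. The retained contrast is then off by (e0 − e1) × D. Under these assumptions, equal removal gives no bias and costs only power.

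The rates and values of D below are assumed; none is in the article.

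- *PIPP change:* e1 = 5%, e0 = 10% to 20%, D = 0.5 to 1 SD. The smallest case is 0.05 × 0.5 = 0.025 SD and the largest 0.15 × 1 = 0.15 SD. At SD 3.4 that is 0.025 × 3.4 = 0.09 to 0.15 × 3.4 = 0.51 points. This SD is quoted in the article for a single PIPP score at a painful procedure, not for a change score.
- *LOS:* a rate difference of 2 to 8 percentage points and D = 10 to 40 days give 0.02 × 10 = 0.2 to 0.08 × 40 = 3.2 days.

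These lines show the mechanism. They do not estimate what would happen in this trial, and the direction for transferred infants is unknown.

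**The case against.** The strongest reply is that this is an ordinary eligibility list. It follows directly on the inclusion criteria and sits among plainly baseline items. No sentence orders the withdrawal of a randomised infant. The plan to record in-hospital complications and have the board compare them implies that infants who develop complications are still followed. Intention-to-treat is named in the main text. A condensed article may also leave the timing of eligibility assessment to the full protocol.

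Most of this stands for enterocolitis, obstruction, surgery and pneumoperitoneum. A reader might infer that these are all events after randomisation, that infants are randomised on day 1, and that applying the list would empty the safety comparison. The documents do not support that: the conditions read naturally as status at screening, the first day is only the earliest time, and removal is nowhere stated.

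A reader might also infer that OMT affects all these exclusions. The Background credits OMT with reducing LOS "as well as the likelihood of gastrointestinal episodes", and says nothing of transfer, surgery or pneumoperitoneum. Likewise, the idea that even an intention-to-treat set would lose these infants supposes that they are re-labelled ineligible, which the article does not say.

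The reply does not dispose of transfer out. That item is written into the list, so it is not a detail left to another document. Given the birth-hospital requirement, it has little work to do unless it is applied after entry.

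**Conclusion.** The point holds for transfer out. A stated exclusion criterion normally takes effect after randomisation and, with a per-protocol primary analysis, removes randomised infants from comparisons that run to discharge. For the other listed conditions there is an ambiguity only: they would add to the problem if applied later, and the text neither orders nor rules that out.

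The size of any bias cannot be estimated from the article, which gives no rates of transfer or of the listed conditions by arm. The firm figure is the allowance: 40 per group covers 7.5% loss, and power falls to 0.792 at 10%. The sample size of 37 per group is correct for its stated inputs. The conclusion rests on reading the transfer criterion as mainly transfer out, and on a per-protocol set leaving out infants who meet an exclusion criterion.

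**What to change.** - Delete transfer to another hospital from the exclusion list.
- State that all exclusion criteria are assessed once, on information available before randomisation.
- State that an infant who is later transferred out or develops a listed condition is analysed in the allocated arm by intention-to-treat for PIPP, LOS, cost and safety, and that a later listed condition counts as a complication.
- Reconcile the analysis set between the Abstract and Statistical analysis, so that intention-to-treat does not depend on which section is read.

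The cost is small. The transfer or discharge date and the last PIPP must be obtained for transferred infants. Keeping them in raises the variance of LOS and cost slightly. The planned 37 and 40 per group do not change.

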### Randomisation and masking

Patients will be randomly assigned in a 1:1:1 ratio to either the OMT, the sham or the control group (Figure 1). Newborns will be eligible for randomisation from the first day of life. Block randomisation will be performed according to a computer-generated randomisation list using a block size of nine, and stratified by OMT group.

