**Flow chart of the study.**

Infants assigned to the study group will be further randomly divided into: OMT group A and OMT group B (Figure 1).

The coordinating centre will perform and store the randomisation list and an external consultant will be in charge of the process. NICU personnel will be unaware of outcome, study design and patients’ allocation. Only osteopaths will be aware of patients’ allocation.

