### Osteopathic procedure

Osteopathic care includes an initial structural evaluation and a final treatment. The structural evaluation is carried out with the newborn lying down in bed and is aimed at diagnosing somatic dysfunctions [19]. The osteopathic manipulative treatment includes the application of a range of manipulative techniques aimed at treating the somatic dysfunctions. Techniques chosen for the present study are balanced ligamentous/membranous tension techniques [15]. The whole session will last 30 minutes: 10 minutes for evaluation and 20 minutes for treatment [15].

OMT will be performed by registered osteopaths with experience in the neonatology field (OMT group A) and final-year students (OMT group B). Newborns allocated to the study group will undergo osteopathic care in addition to usual care.

The sham group will receive only ‘soft touch’, for 30 minutes, plus routine care, whereas the control group will receive routine care only.

Osteopathic care and sham therapy will be administered once a week according to the treatment group. OMT groups A and B will enter the NICU on different days of the week.

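### One fixed, published block size of nine lets anyone who tracks past allocations deduce the end of each block: about 14% of assignments

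*Protocol article*

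**What the plan says.** All references are to the protocol article.

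- Randomisation and masking sets the ratio: "Patients will be randomly assigned in a 1:1:1 ratio to either the OMT, the sham or the control group". The list is a "computer-generated randomisation list using a block size of nine, and stratified by OMT group". The words "using a block size of nine" give the only size; no other is mentioned.
- Methods/design describes one tertiary NICU, and randomisation only after written parental consent. No baseline factor is named as a stratum.
- The text under the flow chart covers concealment and masking. "The coordinating centre will perform and store the randomisation list and an external consultant will be in charge of the process". It also says "Only osteopaths will be aware of" allocation, and that "NICU personnel will be unaware of outcome, study design and" allocation.
- Osteopathic procedure: "Osteopathic care and sham therapy will be administered once a week according to the treatment group". The structural evaluation is done with the infant in bed. OMT and sham sessions both last 30 minutes, controls have no session, and OMT groups A and B attend on different days.
- Trial status describes the research as ongoing, so the block size is public while infants are still being allocated.

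**The concern.** Holding the list centrally hides the list. It does not hide what is left in a block of known length from someone who has followed the earlier assignments. With one site and no prognostic strata there is, on the natural reading, only one sequence to follow, and the article names a group of people who know allocations.

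If someone with that knowledge could influence which family is approached, or when, the likely arm would be known before consent. Randomising after consent does not prevent this. Infants could then differ between arms at entry, for example in gestational age or expected stay, and those differences would feed into PIPP change, length of stay and cost with only 40 infants per arm.

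**Working it through.** The article gives no predictability figure to reproduce. Its sample size (37 per group at f = 0.30, power 0.80, alpha 0.05) does reproduce: one-way ANOVA power is 0.803 at 37 per group and 0.836 at 40. I therefore take N = 120 as given.

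**Inputs.** Block of nine, 1:1:1, so three places per arm per block (Randomisation and masking); N = 120 (Statistical analysis). Assumption: the observer knows the block size, where each block starts, and all earlier allocations.

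**Certain assignments.** The next assignment is certain when all r remaining places belong to one arm. The probability is 3 × C(3, r) / C(9, r).

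| Position | r | Probability certain |
|---|---|---|
| 1–6 | 9–4 | 0 |
| 7 | 3 | 3 × 1 / 84 = 0.036 |
| 8 | 2 | 3 × 3 / 36 = 0.25 |
| 9 | 1 | 1 |

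Sum: 1.286 per block, and 1.286 / 9 = 14.3%. Since 120 = 13 × 9 + 3, and the last three infants fall in positions 1–3, the total is 13 × 1.286 = 16.7 infants.

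**Narrowed assignments.** At position 8 only two places remain, so at least one arm is always excluded. At position 7 all three arms remain with probability 3 × 3 × 3 / 84 = 0.321, so at least one is excluded with probability 0.679.

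**Best guess.** Guessing the arm with most places left is right, at positions 1 to 9, with probability 0.333, 0.375, 0.429, 0.446, 0.471, 0.536, 0.571, 0.625 and 1. The mean is 0.532, against 0.333 by chance.

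**If knowledge lags.** Shift the position figures by the number of latest infants whose allocation is unknown.

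| Latest infants unknown | Certain | Best guess |
|---|---|---|
| 0 | 14.3% | 53% |
| 1 | (0.25 + 0.036) / 9 = 3.2% | 46% |
| 2 | 0.036 / 9 = 0.4% | 43% |

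The lag matters in practice. From 5 May 2014 to 30 September 2015 is 513 days, or 73.3 weeks. That gives 120 / 73.3 = 1.64 infants a week and 9 / 1.64 = 5.5 weeks per block. With weekly sessions, someone relying on visits alone may often be an infant or two behind.

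**Observer who sees only session or no session.** Each block then has six session places and three without. The split is certain with probability 0.012, 0.048, 0.119, 0.25, 0.5 and 1 at positions 4 to 9, which sums to 1.93, or 21% of infants. One infant behind, the sum is 0.93, or 10%. This is certainty about having a session; it does not separate OMT from sham.

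**Varying block sizes.** Simulated lists of 120 infants, with an observer who knows the possible sizes and all past allocations and updates by Bayes' rule:

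| Block sizes | Certain | Best guess |
|---|---|---|
| 9 only | 13.9% | 53% |
| 6 and 12 | 5.6% | 53% |
| 6, 9 and 12 | 2.5% | 53% |

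For nine only, 13.9% is 16.7 / 120; it is below 14.3% because the list ends three infants into a block.

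**The case against.** A permuted block of nine is conventional and fairly long for three arms. Bias needs a person who both follows allocations and influences enrolment, and the article describes no such person. It limits knowledge of allocation to the osteopaths, says unit staff are unaware of it, has the list held centrally under an external consultant, and randomises after consent. The enrolling role may be set out in the full protocol. This stands as a reason to call the matter a risk and to rate it minor. It does not remove the point, because those safeguards protect the list and not the arithmetic of a block whose length is public.

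A reader might infer more than the text supports:

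- **That staff can see who is treated.** The infant is evaluated in bed and no screening of sessions is described, so this is plausible, but the article does not say it. Sight alone would mainly separate infants with sessions from those without.
- **That each osteopath knows the whole sequence.** The article says the osteopaths know allocations, not that each follows every infant. Groups A and B attend on different days.
- **That later assignments are generally predictable.** Certainty about the arm is impossible before position 7 and guaranteed only at position 9.
- **That the results would be biased.** Neither a mechanism nor a size is documented.

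The block structure itself is not fully clear. OMT group is an assigned treatment, not a baseline factor, so stratifying the list by it has no evident meaning. One running 3:3:3 sequence is the natural reading, not a certain one.

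**Conclusion.** The point holds as a minor, cheaply corrected weakness in concealment. With a fixed and published block of nine at one site, a person with complete knowledge of past allocations can deduce about 17 of 120 assignments, always including the last of each full block. This rests on a single 3:3:3 sequence and on complete, current knowledge. One infant behind, certainty falls to about 3%; two behind, to 0.4%. Whether any of it can affect enrolment depends on who screens and obtains consent, which the article does not state. The documents support a risk of selection bias and nothing stronger.

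**What to change.** 1. For infants not yet randomised, have the coordinating centre regenerate the list with block sizes in random order, for example 6 and 12, or 6, 9 and 12. Sizes 6 and 12 contain two or four OMT places, which split evenly into subgroups A and B; the three places in a block of nine do not. Adding size 9 lowers certainty further but gives up that even split.
2. Withhold the sizes from the osteopaths and the unit.
3. State that those who screen and obtain consent are not osteopaths and do not know past allocations. This is needed as well, because varying the sizes does not lower average guess accuracy.
4. Say what stratification by OMT group means, so that the block structure is unambiguous.

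Cost: a short change to the list program and a few sentences in the protocol, with no extra infants. The list has to be reissued and final arm sizes may differ by a few infants. Exact 40/40/40 is not guaranteed now either, since 120 is not a multiple of nine.
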